## Abstract

Current treatments for knee osteoarthritis (KOA) are partially effective. It is, therefore, necessary to find new strategies that can complement the existing ones. In this scenario, transcutaneous vagal stimulation (TVS) neurophysiological effects could be a helpful solution. However, there is no evidence of the efficacy of TVS in KOA. This trial aims to assess the efficacy of TVS in decreasing pain in participants aged 55 years or older with KOA. A randomised controlled, two-arm, double-blind (participants and outcome assessors) and clinical superiority trial will be conducted for 70 patients with KOA. All the participants will carry out an exercise program. It consists of 12 sessions over four weeks. In addition, they will be randomly assigned to (1) active TVS plus physical exercise or (2) sham TVS plus physical exercise. The application of active TVS consists of electronic stimulation of the auricular concha using a portable device. Sham TVS condition consists of the stimulation of the earlobe that does not cause neurophysiological effects. The primary outcome is the reduction in pain intensity. Additionally, functional capacity, physical performance, pain-related interference, pain-related distress, quality of life in older adults and global change will be measured. Assessments will be conducted at the beginning of the study (baseline), at the end of the intervention and after 1 and 3 months of follow-up. This trial will generate evidence regarding the efficacy of TVS in pain perception in individuals with KOA. This information will serve as an input in the clinical decision-making on the use or non-use of TVS in individuals with KOA. Thus, if the efficacy of TVS is confirmed, a new therapeutic tool may be included in the rehabilitation of individuals with KOA.

## 1. Introduction

Osteoarthritis is the most common chronic joint disorder. In this regard, osteoarthritis is the fourth leading cause of disability worldwide in 2020 and the most common joint disease, with knee Osteoarthritis (KOA) being the most common, representing 83% of the total OA burden [1], with most cases presenting chronic pain (i.e., more than 3 months). Thus, several studies report that 90% of the population has had knee pain for more than a year [2]. Thus, KOA is one of the main musculoskeletal health problems in the population [3], affecting 16% in individuals aged 15 and over and was 22.9% in individuals aged 40; the incidence is 203 per 10,000 person years; and the ratios of prevalence and incidence in females and males were 1.69 and 1.39, respectively [4]. KOA entails high health-related costs with subsequent economic expenditures and loss of work productivity [5,6].

For the treatment of KOA, pharmacological treatment had shown limited effects [7,8]. Regarding non-pharmacological treatments, there is no evidence of the benefit of arthroscopic surgery [9,10]. Moreover, physiotherapy-based rehabilitation has shown only partially successful results [11].

A meta-analysis showed that therapeutic exercise programs on land (i.e., not performed in an aquatic environment) provided a short-term benefit for knee pain and functional capacity [12]. However, although rehabilitation is widely accepted as beneficial for KOA, it has demonstrated a small to moderate effect size, similar to standard drug treatment. Consequently, both therapeutic alternatives (i.e., exercise and drugs) show partially effective results with a reduction in pain. Thus, the pain persists, affecting’ patients’ quality of life and work ability.

It is important to note that the mechanisms of chronic pain present in subjects with KOA differ from those with acute pain. Thus, the same nociceptive stimulus may individually cause more pain perception in chronic pain than acute pain. This would be associated with changes in the central nervous system (CNS), which is manifested by a lower intracortical capacity for pain inhibition due to a decrease in the activation of the endogenous system in the modulation of pain [13] regardless of the structural damage caused by the pathology [14]. In this scenario, new techniques have emerged acting on the CNS, such as transcutaneous vagal stimulation (TVS), which has shown an effect in reducing pain [15,16].

TVS belongs to a group of techniques based on neuromodulation. Neuromodulation is a physiological process that consists of an alteration of the neural and synaptic properties of the neurons or substances released by them [17]. Neurostimulation through TVS impacts on the release of neurotransmitters, and thus on the activity of the CNS. In recent years, low-cost, portable, easy-to-use equipment has been developed, which has made it possible to study vagal stimulation in several settings. This technique consists of ‘mild electrical stimulation of the ear’s external surface regions that are innervated by the auricular branch of the vagus nerve.

Pain modulation by TVS has been examined in animals and humans [18,19]. TVS has an impact on the central pain processing centres rather than just peripheral nociceptor activity [18]. Consequently, thick-myelinated fibres of vagus nerve branches that project to the nucleus tractus solitarii and the locus coeruleus in the brainstem are excited. The latter would reach structures related to spinal [20] and supraspinal [21] mechanisms that are involved in the modulation of arousal and pain perception [22]. That descending vagal signals activate anti-inflammatory pathways that suppress pro-inflammatory’ cytokines’ secretion (e.g., TNFα and IL-1β) [23]. In this regard, it has been described the “anti-inflammatory cholinergic pathway” in which efferent vagal fibres are activated by afferent ones (see more information in Lauwers et al., [24]). This becomes relevant in light of findings describing the role of inflammation in Osteoarthritis [25]. On the other hand, studies of TVS in healthy participants [15] with pelvic pain [26] or with chronic headaches [27] have confirmed its effect on pain modulation.

As a critical issue, it should be noted that there is only one study focused on the effectiveness of TVS in osteoarthritis [16]. In this pilot study, the impact of TVS on Erosive Hand Osteoarthritis was studied. The authors found that TVS decreased pain and increased motor function with a reduction of the number of tenderness joints and lower scores in the functional Index for Hand [28].

Thus, this study aims to address this gap in the literature. Specifically, we will study whether TVS could decrease pain and increase functional capacity in a corroborated KOA psychical exercise programme for the knee osteoarthritis (KOA) population. It is important to emphasise that we will focus on KOA as the joint most affected by OA is the knee, which affects 21.7% of women and 11.9% of men over 60 [4].

### Objective

As previously noted, to assess the efficacy of TVS in decreasing pain in participants aged 55 years or older with KOA.

## 2. Materials and Methods

### 2.1. Ethical Considerations and Trial Registration

This project was approved by the Scientific Ethics Committees of the Universidad de La Frontera (ACTA N°120_19) and countersigned by Southern Araucanía Health Service (Folio Numbering-00000040). It was carried out in compliance with the principles of the Declaration of Helsinki [29]. All participants must sign an informed consent form. The data will be registered with code (i.e., participant’s ID) to maintain the participant’s confidentiality. All records with names or other personal information that may identify participants will be kept separately from records with the participant ID. Access to this data will be limited to principal investigators. All records (registration forms and questionnaires) will be stored in a box with restricted access to the research team. All digital files will be kept in a secure computer accessible only to the research team with a password. A complete data backup will be done monthly. After 5 years, the destruction and/or erasure of data shall be carried out.

This study is registered at https://clinicaltrials.gov/ (accessed on 18 October 2022, Trial registration: NCT04381624).

### 2.2. Design

A double-blind, randomised controlled clinical trial will be conducted (See Table 1). The accessible population will consist of participants attending three public health centres in Temuco, Chile. The health centres were selected according to the following criteria: (a) the physical proximity of the centre, (b) they meet regulated standards of practice (i.e., they provide a similar type of social support and health care), and (c) they are the place where our study population receives care, and a sufficient number of patients for our study is ensured. Consolidated Standards of Reporting Trials (CONSORT) [30], The Standard Protocol Items: Recommendations for Interventional Trials reporting guidelines (SPIRIT) [31] and OARSI clinical trials recommendations [32] were implemented in the writing of this protocol.

### 2.3. Assessments

Assessments will be conducted at the beginning of the study (baseline), at the end of the intervention and after 1 and 3 months of follow-up.

### 2.4. Study Population, Recruitment and Assignment

The target population is patients aged 55 and over with a medical diagnosis of KOA [33,34] and chronic pain (i.e., three months or more of knee pain) from primary health centers in Temuco (Chile).

Health care professionals at the health centres will recruit eligible patients during visits or medical care consecutively. They will be referred to health centre staff, who will inform them of the ‘study’s purposes, requesting some means of contact for the research team to communicate with them. Moreover, they will be briefed on the investigation aims and asked if they wish to participate. If the individual agrees to participate, they will meet with the researchers, who will verify enrolment eligibility criteria. When the individual agrees to participate, an initial evaluation of sociodemographic and clinical characteristics will be made. The recruitment period will be extended until the determined sample size is met. One of the investigators will be responsible for continually visiting (i.e., once a month) the health centres in order to monitor the recruitment process.

### 2.5. Groups & Randomisation

Patients will be divided into two groups: an experimental group (active TVS plus physical exercise) and a control group (sham TVS plus physical exercise).

The allocation to the experimental or control group (EG and CG, respectively) will be carried out before starting treatment. It will be made by an external researcher who is not involved in any phase of the study, and only he/she will have full access to this information. Permuted blocked randomisation with a 1:1 randomisation ratio will be performed using Stata v16. Allocation will be concealed using a numbered opaque envelope.

### 2.6. Masking

Participants will be masked as to the study hypotheses, as they will not be informed about the group to which they were assigned. Likewise, the evaluators (who assess at the end of therapy and the follow-up at 1 and 3 months) will not know which group the participants were assigned. Participants and evaluators performing the various assessments will be asked about the group they believe participants were assigned. The masking of evaluators and patients will be maintained until the end of the investigation and data processing. See Figure 1.

### 2.7. Sample Size

Sample size was calculated using G*Power 3 [35], a computer application for computing statistical power analysis. One of the key aspects to determine the sample size was the magnitude of the standardized average effect. According to Tubach et al. [36] the reductions on the VAS responses (the main outcome variable) were large (SD of change = 21.5 mm). Based on this result, we expect a large effect size (0.4 according to Cohen’s *f* criteria; at least 8.6 mm improvement in the VAS). It means a considerable reduction on the VAS responses because the co-intervention (the exercise). Within the F test family, an ANCOVA was selected as a priori statistical test for which the sample size was estimated (two groups, one covariate, Cohen’s effect size *f* = 0.40, α = 0.05, 1 − *β* = 0.80). Based on these assumptions, a total of 64 participants were needed to detect the hypothesized difference between groups. We also expected a 10% dropout rate, so 6 participants were added to the computed sample size (a total of 70 patients; 35 in each group).

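### The sample-size text reads Cohen's f = 0.40 as a standardised mean difference: 80% power does not apply to 8.6 mm, and 64 does not follow from the stated inputs

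*Protocol article*

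**What the plan says.** Section 2.7 takes one SD from a cited study, "SD of change = 21.5 mm", and from it expects a large effect, given as 0.4 on Cohen's f scale and put in millimetres as "at least 8.6 mm improvement in the VAS". It comments: "It means a considerable reduction on the VAS responses because the co-intervention (the exercise". The calculation is then described: "an ANCOVA was selected as a priori statistical test for which the sample size was estimated", with "two groups, one covariate", f = 0.40, α = 0.05 and power 0.80. The result is that "a total of 64 participants were needed to detect the hypothesized difference between groups". On dropout it says: "We also expected a 10% dropout rate, so 6 participants were added to the computed sample size", which makes 70, or 35 per arm.

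Two other places matter. Section 2.5 gives two arms randomised 1:1, both with physical exercise, and section 3.5.2 says the exercise programme is the same in both. Section 3.6 makes the primary analysis an ANCOVA of the 4-week average pain VAS with baseline VAS as covariate.

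**The concern.** The effect size that enters the calculation and the millimetre figure printed beside it differ by a factor of two. The figure of 8.6 mm is the only one in millimetres that a reader can attach to the hypothesised difference between groups, so the text invites the belief that the trial has 80% power for 8.6 mm on the primary outcome. The abstract says the result is meant to inform use or non-use of the device. If the true benefit were about 8.6 mm, a non-significant result would be about as likely as a significant one, or likelier, and the power statement would lend it weight it does not have. The reason offered for a large effect, the exercise given to everyone, is not a reason to expect a difference between the arms.

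**Working it through.** **Inputs.** From section 2.7: SD 21.5 mm, f = 0.40, 8.6 mm, two groups, one covariate, α = 0.05, power 0.80, N = 64 evaluable and 70 randomised. From section 2.5: 1:1 allocation. Not given in the article: the correlation r between baseline and 4-week VAS. It is an assumption below and is shown over a range.

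**1. Where 8.6 mm comes from.** 0.40 × 21.5 = 8.6 mm exactly, so f was multiplied by the SD.

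**2. What f means with two equal arms.** f is the SD of the group means divided by the within-group SD. For two equal arms the SD of the means is half their difference, so f = d/2.
- f = 0.40 gives d = 0.80, a difference of 0.80 × 21.5 = 17.2 mm.
- 8.6 mm gives d = 8.6/21.5 = 0.40, so f = 0.20.

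**3. The plan's own N.** Power comes from the noncentral F distribution with λ = f²N, df1 = groups − 1 = 1 and df2 = N − 3.

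| N | f | df1 | λ | Power |
|---|---|---|---|---|
| 51 | 0.40 | 1 | 8.16 | 79.9% |
| 52 | 0.40 | 1 | 8.32 | 80.7% |
| 64 | 0.40 | 1 | 10.24 | 88.3% |
| 64 | 0.40 | 2 | 10.24 | 80.5% |

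The stated inputs need 52, not 64. Of the variants tried (df1 of 1, 2 or 3, power 0.80 to 0.90, smaller α), only df1 = 2 at 80% power returns 64 exactly, and that does not fit two groups. An α of 0.025 gives 63.

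**4. Power for 8.6 mm with 21.5 mm as residual SD** (the document's own conversion), f = 0.20:
- N = 64: λ = 0.04 × 64 = 2.56, power 35.0%.
- N = 70: λ = 2.80, power 37.8%.
- 80% power would need 199 evaluable participants.
- Solving for 80% power at N = 64 gives f = 0.356, a difference of 2 × 0.356 × 21.5 = 15.3 mm.

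**5. If 21.5 mm is strictly an SD of change.** With equal variances at baseline and 4 weeks, SD of change = σ√(2(1 − r)) and the ANCOVA residual SD = σ√(1 − r²). The residual SD is therefore 21.5 × √((1 + r)/2). The 95% CI half-width is t(0.975, N − 3) × residual SD × √(4/N), with t = 2.000 for N = 64 and 1.996 for N = 70.

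| r (assumed) | Residual SD, mm | Power for 8.6 mm, N = 64 | Half-width, N = 64 | Half-width, N = 70 |
|---|---|---|---|---|
| 0 | 15.20 | 61% | 7.6 mm | 7.3 mm |
| 0.3 | 17.33 | 50% | 8.7 mm | 8.3 mm |
| 0.5 | 18.62 | 44% | 9.3 mm | 8.9 mm |
| 0.7 | 19.82 | 40% | 9.9 mm | 9.5 mm |
| 1 (residual SD = 21.5) | 21.50 | 35% | 10.7 mm | 10.3 mm |

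No r between 0 and 1 brings power for 8.6 mm near 80%.

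**The case against.** The strongest defence is that 80% is formally attached to f = 0.40, not to 8.6 mm. For f = 0.40 the sample is more than adequate, and 8.6 mm is a parenthetical improvement that is not labelled a between-arm difference. It is true that power for f = 0.40 is not overstated. But the text presents the two as the same thing and then refers to the hypothesised difference between groups. If 8.6 mm was meant as improvement within an arm, it is no basis for a between-arm ANCOVA. The equivalence is wrong on either reading.

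A reader might infer that true power is simply 35%. The document does not support that as a single figure. It calls 21.5 mm an SD of change, and baseline adjustment then gives a residual SD of 21.5 mm only at r = 1. A reader might also infer that the confidence interval will always be wider than ±8.6 mm. That fails too: at r = 0.3 the half-width is 8.7 mm with 64 and 8.3 mm with 70.

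The exercise sentence is unclear and may only describe the overall fall in VAS scores. Rewording it would be enough. Section 3.6 already commits to 95% confidence intervals, so misreading of a null result is a risk and not a certainty.

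**Conclusion.** The point stands. Section 2.7 equates f = 0.40 with 8.6 mm when, with two equal arms and SD 21.5 mm, it corresponds to 17.2 mm. The trial does not have 80% power for 8.6 mm. With 64 evaluable, power is about 35% on the document's own use of 21.5 mm as standardiser. It is about 40% to 50% if 21.5 mm is the SD of change and r is assumed to be 0.7 to 0.3, and 61% even at r = 0. The range rests on equal variances at the two visits and on a correlation the article does not give; the shortfall does not depend on which value in the range is right.

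Separately, 64 does not follow from the stated inputs, which need 52. Changing only 8.6 to 17.2 mm would therefore leave a false calculation in place. The co-intervention cannot justify a between-arm effect when both arms receive the same exercise. The size of the trial is not itself shown to be wrong; what is wrong is what the text says that size can detect.

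**What to change.** Keep 70 participants and rewrite section 2.7:

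1. Name the target as a between-arm difference in 4-week average pain VAS, in millimetres.
2. Replace 8.6 mm with 17.2 mm as the equivalent of f = 0.40 at SD 21.5 mm.
3. Replace the statement that 80% power requires 64 with the power the design has. At SD 21.5 mm, 64 evaluable participants give about 88% for 17.2 mm, 80% for about 15.3 mm and about 35% for 8.6 mm. For 8.6 mm, add the 40% to 50% that applies if 21.5 mm is the SD of change and the correlation is 0.7 to 0.3, stating that correlation as an assumption.
4. Remove the co-intervention sentence, or reword it so that it does not support the between-arm effect.
5. State that a non-significant result will be interpreted from the 95% confidence interval and may not exclude an 8.6 mm benefit. The expected half-width with 64 is about 8.7 to 10.7 mm, depending on the residual SD.

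The cost is wording only, with no added participants. The downside is that the stated power for 8.6 mm becomes visibly less favourable.

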### 3.6. Data Analysis

All statistical analyses will be performed using the statistical software program STATA v16. A descriptive analysis of the main variables of the study will be carried out using central tendency statistics (mean, median, mode, etc.) and dispersion statistics (standard deviation, variance, range, etc.). The baseline variables will be reviewed to evaluate the comparability of the groups. The primary outcome measure was the average pain VAS measured at 4 weeks after randomization. TVS was compared with TVS sham using an analysis of covariance (ANCOVA) model that included a TVS sham group as the factor of interest and the corresponding baseline average pain VAS as a covariate. The primary analyses included all available data from all randomized participants. Missing data were accommodated using the technique of multiple imputations. Statistical analyses will be performed according to the intention to treat principle. An alpha level of 0.05 will be accepted as significant. Results will be reported as a minimum between-group mean squared differences and 95% confidence intervals from baseline to end of follow-up.

A secondary analysis compared the percentage of “responders” between groups [51] using a chi-square test. A “responder” was defined as a participant whose VAS pain scores at 4 weeks improvement by at least 20% relative or 15 mm absolute from baseline or was below 40 of 100 [52]. Participants who prematurely discontinued were defined as non responders. Prespecified analyses of secondary outcome variables used similar ANCOVA models to those of the primary analyses. No adjustment for multiplicity was made in the secondary analyses, as they were considered exploratory and hypothesis generating.

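### The stated sample-size inputs give N = 52, not 64, and N, power and effect size cannot be restated until f = 0.40 is reconciled with the printed 8.6 mm

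*Protocol article*

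**What the plan says.** Section 2.7 gives a complete set of inputs. On software: "Sample size was calculated using G*Power 3". On the test: "Within the F test family, an ANCOVA was selected as a priori statistical test". The design entries are "two groups, one covariate", with "effect size *f* = 0.40", alpha 0.05 and power 0.80. The stated result is that "a total of 64 participants were needed to detect the hypothesized difference between groups". For losses it adds: "We also expected a 10% dropout rate, so 6 participants were added to the computed sample size", making 70, or 35 per arm.

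The same section takes an SD of change of 21.5 mm from a cited study and equates f = 0.4 with an improvement of at least 8.6 mm on the VAS.

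The rest of the article fits a two-arm calculation. Section 2.5 describes two groups and "Permuted blocked randomisation with a 1:1 randomisation ratio". The primary model in section 3.6 compares active with sham stimulation, with "the corresponding baseline average pain VAS as a covariate". No third group and no contrast with two degrees of freedom appears anywhere.

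**The concern.** Every input to the F-test calculation is printed, so the result can be checked, and it does not come out. A two-group comparison has one numerator degree of freedom, and at f = 0.40 it needs clearly fewer than 64 participants. The printed N, power and effect size therefore cannot all describe one design.

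At stake is whether the trial's size is justified. Readers and ethics committees re-derive this calculation, and the stated 80% is not the power of this design at the stated f. The effect size is also expressed in two ways that disagree by a factor of two, so repairing N alone could leave a corrected figure attached to the wrong difference in millimetres.

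**Working it through.** **Inputs.** Groups k = 2, covariates c = 1, f = 0.40, alpha = 0.05, power = 0.80, SD of change = 21.5 mm, difference 8.6 mm, dropout 10% (all section 2.7); 1:1 allocation (section 2.5).

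**Method.** Power of the ANCOVA F test from the noncentral F distribution:

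- noncentrality λ = f² × N
- numerator df1 = k − 1 = 1
- denominator df2 = N − k − c = N − 3
- N is the smallest total with P(F′(df1, df2, λ) > F(0.95; df1, df2)) ≥ 0.80.

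**Step 1: try to reproduce 64 from the stated inputs.**

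| N | df2 | λ = 0.16 × N | Power |
|---|---|---|---|
| 51 | 48 | 8.16 | 0.799 |
| 52 | 49 | 8.32 | 0.807 |
| 63 | 60 | 10.08 | 0.878 |
| 64 | 61 | 10.24 | 0.883 |
| 70 | 67 | 11.20 | 0.910 |

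The requirement is 52. Using 0, 1 or 2 covariates does not change it, and a two-sided t test with d = 2f = 0.80 also gives 52. The printed 64 is 12 higher (12/52 = 23%), which is more than rounding.

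**Step 2: what would give 64.**

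- df1 = 2, everything else as stated: power 0.798 at N = 63 and 0.805 at N = 64 with two groups entered; 0.797 and 0.804 with three groups. Either way N = 64 exactly.
- df1 = 1 with alpha = 0.025: N = 63, or 64 in equal arms. This conflicts with the stated alpha of 0.05.

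Among the numerator df tried (1, 2 and 3) at the stated alpha and power, only df1 = 2 returns 64.

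**Step 3: effect size in millimetres.** For two equal arms f = d/2, where d = difference/SD.

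- Printed pair: 8.6/21.5 = 0.40. This is d, so f = 0.40/2 = 0.20.
- Printed f: d = 2 × 0.40 = 0.80, so the difference is 0.80 × 21.5 = 17.2 mm.

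**Step 4: power under each reading.** 70 randomised less 10% leaves 63.

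| Target at SD 21.5 mm | f | N for 80% | Power at 63 | at 64 | at 70 |
|---|---|---|---|---|---|
| 17.2 mm | 0.40 | 52 | 88% | 88% | 91% |
| 8.6 mm | 0.20 | 199 | 35% | 35% | 38% |

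With 63 evaluable, 80% power is reached at f ≈ 0.359, a difference of 2 × 0.359 × 21.5 ≈ 15.4 mm.

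**Step 5: sensitivity of the 8.6 mm row.** It assumes a residual SD of 21.5 mm. The article gives no baseline correlation. If 21.5 mm were instead an outcome SD reduced by the covariate (an assumption, since it is stated as an SD of change), f becomes 0.20/√(1 − r²). For r = 0.5 the requirement is 150 and power at 64 is 44%; for r = 0.7 these are 103 and 60%.

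**The case against.** The strongest reply is that the discrepancy is conservative. At f = 0.40, 64 exceeds 52, power is 88% rather than 80%, and neither recruitment nor analysis would change. That stands as far as it goes: taken alone, the N error costs no power.

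A reader might infer from it that the trial is comfortably oversized, that 70 is confirmed as adequate, or that recruitment could fall towards 52. The document does not support any of these. Each holds only if 17.2 mm is the intended difference, and the only difference in millimetres that the article prints is 8.6.

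A reader might also infer that someone entered two numerator degrees of freedom, or three groups. The match is exact, but the article states no numerator df and shows no software entry, and a different alpha comes close. It remains a likely explanation and not an established one. That 64 does not follow from the stated inputs does not depend on it.

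Finally, the dropout step could be called a second error, because 70 less 10% leaves 63 and 64/0.9 = 71.1, or 72 in equal arms. This is a side note. It measures the shortfall against a 64 that the inputs do not support, and 63 against 64 moves power at f = 0.40 only from 88.3% to 87.8%.

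**Conclusion.** The concern holds. The inputs in section 2.7 give 52, not 64, and at the printed f the power is 88.3% with 64, 87.8% with 63 and 91.0% with 70, against a stated 80%. This rests only on the printed inputs and the standard noncentral F calculation, so confidence is high. Two numerator degrees of freedom is a plausible cause and is unconfirmed.

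What the trial's real power is cannot be settled from the document, because f = 0.40 and 8.6 mm describe different targets. If 17.2 mm is meant, power with 63 evaluable is about 88%. If 8.6 mm is meant, it is about 35% at a residual SD of 21.5 mm, and higher only to the extent that baseline adjustment brings the SD below that value. The statement is wrong as written and should be corrected; the finding is neither evidence of oversizing nor an endorsement of 70.

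**What to change.** Rewrite section 2.7 in this order.

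1. State the between-group difference in millimetres that the trial is meant to detect and the SD used, and derive f from them as difference/(2 × SD). Remove whichever of f = 0.40 and 8.6 mm does not belong.
2. Recompute with one numerator degree of freedom, and state that value in the text.
3. Report the requirement and the power for 70 randomised and about 63 evaluable. If the target is 17.2 mm: 52 required, about 88% power, and 80% power at about 15.4 mm. If it is 8.6 mm with SD 21.5 mm and no further variance reduction: about 199 required and about 35% power. Any gain claimed from baseline adjustment needs a stated and justified correlation.
4. Until step 1 is settled, do not quote 88% power and do not use 52 to reduce recruitment.
5. In passing, make the dropout sentence agree with its 10%.

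The correction itself costs wording only. If 8.6 mm proves to be the target, the size of the trial becomes a separate decision for the sponsor.
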